# Preventive health examinations: protocol for a prospective cross-sectional study of German employees aged 45 to 59 years (Ü45-check)

**DOI:** 10.3389/fpubh.2023.1076565

**Published:** 2023-06-12

**Keywords:** screening, prevention, rehabilitation, medical health examinations, disability pension, Ü45-check

## Abstract

**Objective:**

Early identification of health-related risk factors is of great importance for maintaining workability. Screening examinations can help to detect diseases at an early stage and provide more needs-based recommendations. This study aims (1) to assess the individual need for prevention or rehabilitation based on preventive health examinations compared to a questionnaire survey, (2) to assess the results of the preventive health examinations compared to the Risk Index – Disability Pension (RI-DP), (3) to assess the results of the questionnaire survey compared to the RI-DP, (4) to assess the general health status of the sample (target population > 1,000) in German employees aged 45–59, (5) to identify the most common medical conditions. A further study question aims, and (6) to investigate the general health status of the specific occupational groups.

**Methods:**

Comprehensive diagnostics including medical examination, anamnesis, anthropometric measurements, bioelectrical impedance analysis (BIA), handgrip strength, resting electrocardiogram (ECG), resting blood pressure, pulse wave velocity (PWV), and laboratory blood analyses added by a questionnaire are conducted. The research questions are analyzed in an exploratory manner.

**Results and conclusion:**

We expect that the results will allow us to formulate recommendations regarding screening for prevention and rehabilitation needs on a more evidence-based level.

**Clinical Trial Registration**: DRKS ID: DRKS00030982.

## Introduction

Demographic change is a topic that is not only being discussed in Germany today but has been known for decades. High-birth-rate cohorts such as the baby boomers will retire or take early retirement in the near future. The shrinking population in Germany and the demographic aging are increasing challenges for the healthcare system and the social insurance system (1). The COVID-19 pandemic may have led to a rise in early labor cessation in the baby boomer generation, which represents an additional challenge (2).

Various diseases can lead to incapacity for work. Some of the risk factors can expand unnoticed over decades, namely an unhealthy diet, smoking, excessive alcohol consumption, and a lack of physical activity. Overweight and obesity numbers have risen in industrialized countries in recent years (3). Due to the high number of risk factors, specific prevention and rehabilitation measures should be developed to prevent and reduce diseases (4). Screening examinations are encouraged to determine an individual’s risk of developing diseases. In order to find out which program or therapy is individually appropriate, health checks should be performed. It is important that public healthcare institutions provide information about screening examinations and ensure access (5). The focus should be on education regarding the early detection of diseases so that individuals are able to evaluate the benefits and participate in screening examinations. It is important to target asymptomatic individuals to detect possible diseases at an early stage (6, 7) as non-communicable diseases, like cardiovascular diseases, are the leading cause of mortality globally (8) and account for 40% of all deaths (9). Screening examinations could assess the risk of developing cardiovascular disease in Germany (6).

For a feasible and effective screening, a comparison of different screening models is required. While screening examinations were once dismissed as unimportant because of their little yield, in recent years they have moved more into focus again. The reason for this is that screenings are being developed in a more targeted manner, such as precisely for pre-symptomatic individuals or certain age groups (10).

The study ‘Ü45-Check’ addresses interests and questions from the fields of politics, medicine, and science. In 2016, a pension law (11) was passed in Germany that allows a more flexible entry into retirement, following the Scandinavian model (12). Three political parties (Social Democratic Party of Germany (SPD), Alliance 90/The Greens (Bündnis 90/Die Grünen), and Free Democratic Party (FDP)) have formed a coalition in Germany in December 2021. In the coalition agreement for 2021–2025 (13), a paragraph on prevention and rehabilitation has been written, stating that healthier working should be the focus of pension policy. The associated principle ‘prevention before rehabilitation before retirement’ promises simplified access to prevention and rehabilitation programs. Following this, the present study is listed in the coalition agreement for 2021–2025 on page 58 (13).

The challenge of simplifying access to prevention and rehabilitation programs is of particular interest to public health reducing sick leave and disability pensions potentially leading to higher costs for the social insurance systems, such as the German Pension Fund (GPF) (14, 15).

To gain further insight into the characteristics of disability pension applicants, a risk level prediction index was developed in a previous research project. Bethge et al., 2011 (16) developed the Risk Index – Disability Pension (RI-DP). They identified variables of prognostic relevance for disability pension in the register data of the GPF and constructed a risk index for work disability that is applied in the present study.

The primary aim of this study is to assess the need for prevention or rehabilitation based on preventive health examinations compared to a questionnaire survey by another research group (17, 18). As secondary aims, we, first of all, want to examine the influence on relationship between the medical examinations, the questionnaire, and the RI-DP on a disability pension. As further secondary aims, we are interested in assessing the general health status of the sample of German employees aged 45–59. Thereby, we are interested in the most common medical conditions, the health status of the specific occupational groups, and the need for rehabilitation.

### Primary study question

1. Are there differences in the assessment of the need for prevention or rehabilitation based on the preventive health examinations compared to accessing the need for preventive or rehabilitation measures by a questionnaire survey?

### Secondary study questions

2. Is there any relation between the results of the preventive health examinations and the RI-DP Index (traffic light systems)?3. Is there any relation between the results of the questionnaire survey and the RI-DP Index (traffic light systems)?4. What is the general health status of the sample of German employees aged 45–59?5. Which diseases are most common in the sample?6. What is the general health status of specific occupational groups?

## Methods/study design

### Study design and population

This study is designed as a cross-sectional trial to investigate the implementation and evaluation of preventive health examinations offered to adults aged 45 to 59 years in Berlin and Brandenburg, Germany. Administratively, all persons insured by the GPF who were between 45 and 59 years old and living in Berlin or Brandenburg in June 2021 were identified in the GPF Registers and allocated to one of three groups in terms of risk for work disability [see *Risk Index – Disability Pension* (*RI-DP*)]. The subjects (target population > 1,000) will be randomly selected from each of the three groups and will be invited to attend the preventive health examination (Ü45-Check) in the following two consecutive calendar years (2021 to 2023) (Figure 1).

**Figure 1 fig1:**
[figure not shown]
Study flow diagram, Ü45-Check; Germany 2022; Risk Index – Disability Pension (RI-DP).

### Inclusion criteria

Insured persons of GPF, residence in Berlin or BrandenburgAge of 45 to 59

### Exclusion criteria

Insufficient skills in German language or English languagePersons who are already in early retirementPersons who have recently had a rehabilitation treatment

### Recruitment and invitation

All subjects will receive a postal invitation from the GPF including information about the objectives of the Ü45-Check health examination. Subjects can voluntarily contact Charité – Universitätsmedizin Berlin by phone or email to schedule an appointment. A suggested appointment time is provided. The scheduled time may be accepted, modified, or rejected via phone or email. Three months after the postal invitation, the subjects receive a letter for the evaluation of the Ü45-Check. The evaluation is part of another research group.

### Risk index – Disability pension

The study of the RI-DP was designed as a case–control study of the GPF using data from 8,500 men and 8,405 women. Independent samples (control group) were used to validate their models. The information revealed by that index can be used to enhance the provision of rehabilitation programs. The RI-DP can be calculated based on secondary data for the 3 years preceding the reference year. A person has a high risk of disability pension if the RI-DP is ≥60, a moderate risk is <60 und ≥ 50, and a low risk is <50 (16, 19).

In our study, the RI-DP is collected and considered during recruitment. It does not influence the study participation or non-participation. Physicians and study participants do not have any information about the respective index value (of the subject), only the project management does.

### Setting

The preventive health examinations are performed in the outpatient clinic of the Department of Sports Medicine, Charité – Universitätsmedizin Berlin/Humboldt-Universität zu Berlin. Charité – Universitätsmedizin operates as an independent contractor within the public health service and is remunerated based on a combination of fee-for-service.

### Questionnaire (Ü45-screening)

Before the health examination, subjects are asked to answer a web-based questionnaire, which may be completed in approximately 10 min. The questionnaire was developed by another research group in 2019, as part of the Ü45-Check (17, 18). The questionnaire includes five dimensions adapted from already established questionnaires, which have been proven to help identifying an already existing limitation of the ability to work or predict a hazard. The questions relate to dimensions of workability, mental health, functional ability, coping behavior, and sports and exercise behavior (Table 1). Items were reused from the Work Ability Index (WAI) (20), SIMBO (21), PHQ-4 (22), IRES-3 (23), and General Practice Physical Activity Questionnaire (GPPAQ) (24). The questionnaire can be found in Supplement S1. Subjects are informed about the opportunity for responding to the questionnaire together with study staff if support is needed for any reason.

**Table 1 tab1:** Ü45-Screening questionnaire.

	Measurement	Technical information
Questionnaire	**Ü45-Screening** Work ability Mental health Functional ability Coping behavior Sports and exercise behavior	IPAD 6th generation, Apple, U.S.

The questionnaire is evaluated using a point system, accordingly, different values depending on the answer to each question, and dimensions are evaluated separately and weighted differently. Further details can be found here (17, 18). Three domains are categorized in the questionnaire evaluation: no action needed, prevention program suggested, and rehabilitation program suggested. Accordingly, ‘need for action’ (e.g., rehabilitation program suggested in the dimension of ‘workability’) is present when the score reaches more than half of the possible points (≥ 7 of 12 possible points). Prevention program in the dimension of ‘work ability’ is recommended if the score reaches 1/3 of all possible points (≥ 4 points) (17, 18).

### Preventive health examination

The health professionals at Charité – Universitätsmedizin Berlin will perform the clinical examination. The examination in total takes approximately 120 min including the following diagnostics: Anthropometric measurements, bioelectrical impedance analysis (BIA), handgrip strength, systolic and diastolic blood pressure (SBP and DBP) (25), resting electrocardiogram (ECG), and pulse wave velocity (PWV) (26). The subjects will wear underwear during instrumental diagnostics.

Details about the diagnostics and measurements are given in Table 2.

**Table 2 tab2:** Measurements in preventive health examination Ü45-Check.

Clinical measures	Measurement	Technical information
Anthropometry	**Height (cm), Weight (kg)** Body-Mass-Index (BMI) (kg/m^2^)	Seca 274 Stadiometer, Seca, Germany
	**Waist (cm), Hip (cm)** Waist-to-Hip-Ratio (WHR) (Waist cm/Hip cm)	Seca 201 measuring band, Seca, Germany
Body composition	**Bioelectrical Impedance Analysis (BIA)** Percent body fat (PBF), Fat free mass (FFM), Visceral fat area (VFA), Total body water (TBW), Intracellular water (ICW), Extracellular water (ECW), Phase angle (PhA)	InBody 770, Inbody, South Korea
Handgrip strength diagnostics	**Handgrip Strength** (2 times each hand)	Hand dynamometer Lite, Baseline Evaluation Instruments, Germany
Cardiovascular diagnostics	**Twelve-lead Resting Electrocardiogram (ECG)**	Custo cardio 400, Custo med, Germany
Vascular diagnostics	**Blood Pressure (BP)** Systolic blood pressure (SBP) Diastolic blood pressure (DBP)	Classic III Stethoscope, 3 M Littmann, U.S.; boso med I, BOSCH + SOHN GmbH, Germany
	**Pulse Wave Velocity (PWV)** **Pulse Wave Analysis (PWA)**	Vicorder, SMT, Germany
Anamnesis	Chronic or current symptoms, medical history, family history, medication, dietary habits/supplements Cardiovascular risk factors, activity and training	IPAD 6th generation, Apple, U.S.
Cardiovascular examination	Cardiac examination Pulmonary examination Abdominal examination Peripheral vascular Examination	CORE Digital-Stethoscope, 3 M Littmann, U.S.
Blood sampling and analyses	**Blood Analyses** Blood cell and differential cells count, electrolytes, C-reactive protein (CRP), liver enzymes (GOT (AST), GPT (ALT), gamma-GT), blood lipid levels (total cholesterol, HDL-cholesterol, LDL-cholesterol and triglycerides), renal function parameters, ferritin, fasting glucose, Glycosylated hemoglobin (HbA1C), thyroid-stimulating hormone (TSH), urine test strip	

In the following consultation with a physician, a careful anamnesis regarding the relevant medical history is conducted. As most days missed at work are due to cardiovascular, orthopedic, or mental illness, former medical reports are screened for relevant cardiopulmonary, orthopedic, or psychosocial diseases or risk factors. Furthermore, medical needs and current health problems addressed, giving advice on further treatment and evaluation. In addition information about regular exercise/physical activity, health-relevant habits, as well as a healthy diet, is given.

The physical examination will focus on the cardiovascular system, lungs, and abdomen. The blood analyses will be taken under fasting conditions. These include screening parameters for diabetes, lipid profile, inflammatory markers as well as liver enzymes, and thyroid hormones. In addition, a urine sample is screened for proteinuria, hematuria, leukocyturia, and other abnormal parameters (Table 2).

### Assessment of body composition

A non-invasive bioelectrical impedance analysis (BIA) will be conducted to estimate body composition. Well-trained study staff will perform the measurement according to the standardized procedure. Subjects will be instructed to abstain from caffeine and alcohol for 24 h, and exercise for 12 h before testing according to published guidelines for BIA (27). Multiple frequencies at 5, 20, 250, and 500 kHz will be used to measure intracellular and extracellular water separately. The subjects will be measured under laboratory conditions standing barefoot, in underwear, and without wearing jewelry on the device. With abducted arms 15° and legs 45° apart, they will hold a hand electrode with a contact of all 10 fingers while heels and forefeet will be placed appropriately on the foot electrode. Then, an alternating current of 250 mA of intensity will be applied to measure the impedance of the arm, trunk and leg muscles. Whole-body resistance will be calculated as the sum of segmental resistance (right arm, left arm, trunk, right leg, left leg). The BIA with InBody 770 (Seoul, Korea) has been validated by dual-energy X-ray absorptiometry (28). In normal and overweight adults, multiple frequency BIA underestimated the percentage of body fat within the precision of the BIA instrument (2%) (27, 28).

### Assessment of handgrip strength diagnostics

The handgrip strength diagnostics is measured by a research assistant using a hand dynamometer (Baseline Evaluation Instruments, Germany) (29). Subjects are encouraged to squeeze a hand dynamometer as hard as possible using one hand. Handgrip strength is measured in a seated position with the elbow flexed at 90°, adjacent to the torso, and the thumb facing upward. Each hand is tested twice, alternating hands between trials with a 1-min rest between tests on the same hand (30).

### Assessment of (cardio) vascular diagnostics

A Twelve-lead resting electrocardiogram (ECG) (Custo Cardio 200 Saug-EKG, Custo med GmbH, Ottobrunn, Germany) is performed.

First, the blood pressure is measured on both arms using the device (Vicorder, SMT Medical Technology GmbH, Germany). Then the pulse wave analysis is performed on the right upper arm, while the cuff is inflated to the diastolic pressure. In preparation for the PWV examination, a standard cuff is placed at the upper thigh on the right leg. Subsequently, a special collar is placed at the lateral right side of the neck over the common carotid artery region.

### Traffic light system

Immediately after the Ü45-Check, the subject’s health condition is assessed by physicians in a traffic light system. The study physician determines the health status based on the medical history and the examination results, but without knowing how the result of the questionnaire (Ü45-Screening) turned out. The subjects receive the results of each measurement and overall assessment of their health condition. Further examinations are needed and recommendations are offered stratified by the risk profile of the individual (Figure 2).

**Figure 2 fig2:**
[figure not shown]
Study flow diagram, Ü45-Check Traffic light system; Germany 2022.

## Statistical methods

All analyses will be conducted in an explorative setting. In the first step, a descriptive analysis will be performed summarizing all variables with absolute and relative frequencies for categorical variables, and means and standard deviations for continuous variables. Based on the primary study question, the hypothesis is that the assessment based on preventive health examinations differs from the assessment according to the Ü45-questionnaire. Hence, for the primary endpoint, the score according to the Ü45-Screening questionnaire will be evaluated first. Afterward, the results of the classification of patients into green, yellow and red based on the Ü45-Screening questionnaire are compared with the classification according to the physician’s assessment. Therefore a Stuart-Maxwell test will be used to test for marginal homogeneity and a weighted kappa coefficient using linear weights will be calculated. In the second step, the differences between the results based on the Ü45-Screening questionnaire and the medical assessment will be visualized using boxplots and histograms for all variables based on the clinical examination and the questionnaire, respectively. In addition, these variables are used to build two ordinal regression models, one that uses the physician’s assessment as the dependent variable and one with the assessment by the Ü45-Screening questionnaire as the dependent variable. In each case, the green category is used as a reference. The two regression models are compared to determine the factors influencing the various ratings. Secondary aims (2) and (3), which aim to compare the assessment by means of the Ü45-Screening questionnaire and the medical assessment with the RI-DP index, respectively, will also be assessed by visualization for all variables using boxplots and histograms. Since the RI-DP index measures a different outcome from the assessment by the Ü45-Screening questionnaire and the medical assessment, a statistical test will not be used.

In order to assess the general health status of the sample, the variables of the anamnesis and the clinical examination are of main interest. Those variables are analyzed descriptively with absolute and relative frequencies for categorical variables, and means and standard deviations for continuous variables. In addition, this is also conducted as a subgroup analysis for different occupations. In order to assess which diseases are the most common in the sample, the absolute and relative frequencies of each disease are calculated and compared.

If missing values are present, their structure is analyzed and based on this, multiple imputation is considered.

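### The ordinal model for the questionnaire rating uses the questionnaire's own variables as predictors, so it re-describes the scoring key and the planned comparison with the physician model adds nothing

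*Protocol article*

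**What the plan says.** The Statistical methods section first plans the Stuart-Maxwell test and a linearly weighted kappa on the two three-level classifications. In a second step it plans plots of the differences "for all variables based on the clinical examination and the questionnaire, respectively". It then continues: "In addition, these variables are used to build two ordinal regression models". One model has the physician's assessment as outcome, and the other is "one with the assessment by the Ü45-Screening questionnaire as the dependent variable". The purpose is given as: "The two regression models are compared to determine the factors influencing the various ratings".

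The Questionnaire (Ü45-screening) section explains how the second outcome arises: "The questionnaire is evaluated using a point system, accordingly, different values depending on the answer to each question". For the work-ability dimension it gives the cut-offs. Rehabilitation is suggested when "the score reaches more than half of the possible points (≥ 7 of 12 possible points", and prevention "if the score reaches 1/3 of all possible points (≥ 4 points". Dimensions are scored separately with different weights, and the article refers to two cited sources for the rest. It does not show how the five dimensions combine into one class.

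The Traffic light system section says that the physician rates from history and examination without knowing the questionnaire result. The Strengths section counts the ordinal regression of influencing factors among the advantages of the sample size.

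**The concern.** The two outcomes differ in kind. The physician's colour is a judgement, so asking which findings go with it is an empirical question. The questionnaire's colour is a calculation from the answers, so asking which answers go with it has a known reply: those to which the key gives points. The text places the answers among the predictors of their own score, and nothing in the article takes them out again.

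The primary study question is whether the two assessments differ. The Stuart-Maxwell test and kappa address whether and how much they do. Apart from the plots, these two models are the only planned analysis of why. As described, the comparison would show questionnaire answers driving the questionnaire rating and clinical findings contributing nothing to it. That pattern follows from the design of the score, but it could be reported as a finding about how physicians and the questionnaire weigh health problems.

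**Working it through.** The article gives no power or precision figure for this analysis, so there is none to reproduce. The check is a structural argument followed by a simulation.

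**Inputs from the article.** Predictors: clinical and questionnaire variables (Statistical methods). Second outcome: the class from a point system, with work-ability cut-offs at 4 and 7 of 12 points (Questionnaire section). These match the stated fractions: 4/12 = 1/3, and 7/12 = 0.58, which is above one half. Target sample: more than 1,000 (Study design and population).

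**Step 1: clinical variables have no effect given the answers.** Let A be the answers, C the clinical variables and Q = g(A) the questionnaire class. Then P(Q = k | A, C) equals 1 if g(A) = k and 0 otherwise. C does not appear. This holds for any scoring rule g.

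**Step 2: when the estimate is not finite.** The proportional-odds model is logit P(Q ≥ k) = β′A + γ′C − θ_k. Suppose the class is a cut of a linear score w′A, with thresholds 3.5 and 6.5 separating integer points at 4 and 7. Put β = t·w, γ = 0 and θ_k = t × threshold. A person with 4 points then has P(Q ≥ prevention) = 1/(1 + exp(−0.5t)). This is 0.993 at t = 10 and 0.99995 at t = 20. The likelihood rises with t without reaching a maximum (complete separation). If the class is set by the worst dimension, max(A) is not a linear score and this argument does not apply.

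**Step 3: simulation.** Assumptions: n = 1,000; five dimensions of 0 to 12 points; four clinical variables sharing a latent health factor with the dimensions; physician rating built from clinical variables plus noise; three random seeds; three assumed scoring rules. Separation was tested by linear programming.

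| Assumed rule | Separated at both cuts | McFadden R², dimension scores only | R², scores plus clinical |
|---|---|---|---|
| Work-ability cuts 4 and 7 alone | yes, every seed | 1.000 | 1.000 |
| Weighted sum of dimensions | yes, every seed | 1.000 | 1.000 |
| Worst dimension, cuts 4 and 7 | no | 0.501, 0.524, 0.522 | 0.502, 0.527, 0.522 |

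Under the first two rules the coefficients had run to between 85 and 453 when the optimiser stopped, and these values are not estimates. Under the third rule 77% to 79% were classified correctly. Clinical variables added at most 0.527 − 0.524 = 0.003 to R². The remaining misfit is functional form, not clinical information.

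The physician model on both variable sets could be fitted: R² 0.35 to 0.37, clinical z 5.3 to 14.5, questionnaire z between −1.5 and 1.8. The near-zero questionnaire effects were built into the simulation. The run shows only that this model can be estimated.

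**Step 4: the other reading.** The word 'respectively' might mean that each model takes only its own variables. The second model is then purely the scoring key, and the two models have no predictor in common whose effects could be set side by side.

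**Step 5: leaving the screening variables out.** With clinical variables alone as predictors of the questionnaire class, there was no separation under any rule. R² was 0.08 to 0.22, 60% to 77% were classified correctly, and z was 3.3 to 8.1. The model then estimates something the key does not already fix.

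**The case against.** The strongest reply is that this is an exploratory second step. The primary question is answered by the Stuart-Maxwell test and the weighted kappa, neither of which uses the models. That stands, and it limits the severity. It does not rescue the second model: an exploratory label excuses low power or many comparisons, not a regression whose answer is fixed beforehand.

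Four stronger readings are tempting, and the article does not support them:

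- **The model must fail to converge or reproduce the key exactly.** The article gives cut-offs for one dimension only and leaves the combination rule to cited sources. A worst-dimension rule fits the statement that dimensions are scored separately, and it showed no separation.
- **Nothing about disagreement can be learned.** The physician model, read against the published key, is informative about what drives the physician's rating. Boxplots and histograms of the differences are also planned.
- **Models that share no predictors cannot be set side by side at all.** Each rating's correlates can still be described. What is missing is a contrast for the same factor.
- **A factor significant in one model but not the other will be taken as a rater difference.** The article names no such rule. If it were used, the risk would depend on the true effect. With equal effects in both ratings, n = 1,000 and an assumed shared person effect of SD 1, one model was significant and the other not in 7% of samples at log odds ratio 0, 44% at 0.10, 37% at 0.17, 5% at 0.30 and 0% at 0.40 (150 samples each). A second run gave 26% at 0.08, 45% at 0.17 and 4.5% at 0.30. The range is about 0% to 45%, and nothing in the article selects a value within it.

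**Conclusion.** The point holds for the second ordinal model and for the comparison built on it. The circularity follows from the article's own description of the predictors and the score, on either reading of the sentence and under any scoring rule. Whether the model also lacks a finite estimate depends on the rule, which is not shown: yes under a single-score or weighted-sum rule, no under a worst-dimension rule. The simulated R² values rest on the assumed data structure and illustrate the mechanism; they do not predict the study's results.

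The damage is confined to the only planned model-based explanation of why the ratings differ. The primary test, the kappa, the plots and the physician model taken alone are unaffected. This should be fixed, but the primary result does not depend on it.

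**What to change.** 1. Use one common predictor set for both ratings, leaving out all Ü45-Screening items and dimension scores: age, sex, occupation, history, clinical and laboratory measures. An anamnesis field that repeats a screening item should be left out too.
2. Replace the comparison of two separate fits by a single analysis. One option is to model signed disagreement (questionnaire higher, same, physician higher). The other is a stacked ordinal model with two rows per person, rater-by-factor interactions and person-clustered standard errors. Either suffices.
3. Report the disagreement or interaction estimates with confidence intervals, and describe them as associations.
4. Show the questionnaire dimensions descriptively by disagreement category.

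The cost is a change of wording and slightly more analysis. No new data are needed. By the article's own account, 660 participants had been screened by April 2023 and recruitment was to run to March 2024.
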